### Randomization and blinding

Randomization sequence will be generated by a designated staff not involved in outcome data collection and analysis, who will use the block randomization method via SPSS version 22.0 (International Business Machines Inc., USA), with an electronic table of random numbers to allocate eligible participants to either of the two groups (in a 1:1 ratio). The allocation sequences will be prepared and be kept inside sealed, opaque, and consecutively numbered envelopes. The envelope will be opened by the neurosurgeons in charge, who will then prepare the study solution based on the respective allocation scheme and be therefore made aware of group assignations. Participants will be enrolled by a dedicated research nurse not involved in the data collection and analysis, and the neurosurgeons in charge are responsible for assigning participants to interventions. This is an open-label design with only patients and independent researchers in charge of follow-up and data analysis blinded to allocation. The D-PAL is a lipid emulsion in the infiltration solution, which can be easily distinguished from the clear ropivacaine alone study solution. Therefore, unblinding will not occur.

Prior to the commencement of the study, all investigators will receive standardized training on trial content, treatment strategies, evaluation, and quality control. All interventions will be carried out in accordance with clinical practice guidelines. During preoperative visit, eligible patients should be acquainted with pain NRS ranging from 0 (no pain) to 10 (worst possible pain) [31]. They will be guided on how to use a patient controlled analgesia (PCA) device.

### Intervention description

The neurosurgeons in charge will be responsible for the preparation of the respective drugs in a sterile fashion: 2 mL D-PAL emulsion (4.0 mg as D-PAL/mL is equivalent to 2.5 mg as dexamethasone; by Mitsubishi Tanabe Pharma Korea Co., Ltd) and 15 mL of 1% ropivacaine (Nai Le Pin ® 10mg/mL; by AstraZeneca AB, Sweden) diluted to a total volume of 30 mL in normal saline for ropivacaine plus D-PAL group, and 15 mL of 1% ropivacaine diluted to a total volume of 30 mL in normal saline for ropivacaine alone group.

### Anesthesia management

All patients will follow a standard anesthesia technique. In the operating room, standard monitoring will be continuously established, which includes electrocardiography, pressure (BP), heart rate (HR), pulse oxygen saturation (SpO_2_), bispectral index (BIS), and temperature. All patients will be preoxygenated with FiO_2_ > 0.8 before anesthesia induction with intravenous midazolam 0.05 mg/kg, sufentanil 0.3-0.5 μg/kg, propofol 1.5-2 mg/kg, and cisatracurium 0.2 mg/kg. After endotracheal intubation, anesthesia will be maintained with sevoflurane (0.4 MAC) and propofol (2-4 mg/kg∙h) to keep BIS values 40-60. The ventilation protocol consists of volume-controlled mechanical ventilation (Datex Ohmeda S/5 Advance, General Electric Healthcare, Helsinki, Finland) with an air-oxygen mixture (60:40), TV of 6-8 mL/kg, inspiratory to expiratory ratio of 1:2, fresh gas of 1-2L/min and a respiratory rate adjusted to normocapnia (PaCO_2_ between 35 and 45 mmHg). Intraoperative analgesia will be provided with continuous remifentanil infusion (0.1-0.3 μg/kg∙min) until the removal of Mayfield head holder at the end of surgery. Remifentanil infusion dose will be adjusted to attenuate potent stress responses and to keep mean arterial pressure (MAP) and HR within ± 20% of baseline values. Tramadol 100 mg will be administered intravenously before skin closure to prevent postoperative shivering and remifentanil-induced hyperalgesia, and ondansetron 4 mg will be given simultaneously to prevent tramadol-induced nausea and vomiting. No additional analgesics and antiemetics will be administered intraoperatively. Intraoperative hypertension and/or tachycardia will be treated with esmolol 0.5 mg/kg or nicardipine (10 μg/kg). Bradycardia (< 50/min) will be treated with atropine bolus 0.01 mg/kg. Muscle relaxants will be used as needed intraoperatively and the residual neuromuscular block will be antagonized with neostigmine 0.04 mg/kg and atropine 0.02 mg/kg after spontaneous ventilation recovery postoperatively. Patients will be shifted to the Post Anesthesia Care Unit (PACU) for monitoring after successful extubation, with stable hemodynamic, respiratory, and neurologic conditions.

### Pre-incisional infiltration

Patients will receive pre-emptive infiltration by the neurosurgeon immediately before head fixation in a sterile fashion. A 22-gauge needle will be introduced into the planned incision site, as well as each pin fixation site of the Mayfield head holder, at a 45° angle and throughout the entire thickness of the scalp. The ropivacaine plus D-PAL group will receive 0.027% D-PAL and 0.5% ropivacaine, whereas the ropivacaine alone group will be injected with 0.5% ropivacaine alone. The total volume of the local infiltrated solution will be at the discretion of the neurosurgeon, based on the length of the incision.

### Additional interventions

Patients will be evaluated to check fitness for NRS assessment 1 h after shifting to PACU, using a modified questionnaire of the Short Orientation Memory Concentration (SOMC) test [32]. The cognitive function of patients will be rated as good, able to recall and count with minimal mistakes (1-3); fair, with ≥ 3 mistakes; and poor, not able to recall at all. For patients regarded as poor, the same test will be repeated 1 h later. If the grading is poor again, then that patient will be withdrawn from the study [33]. A  PCA device containing sufentanil 200 μg and ondansetron 16 mg in 100 mL saline will be set up to deliver 1 mL as an intravenous bolus with a 10-min lockout interval after craniotomy. The maximum dose will be limited to 8 μg per hour, and there will be no initial dose or background infusion. Patients will be advised to push the analgesic demand button if they feel pain and to repeat it until the pain is relieved. PCA regimen will be discontinued when it is no longer needed. Each press will be recorded by an electronic memory system, including both valid and invalid presses. Patients will be given an oral supplementary tablet of oxycodone (OC)/acetaminophen (APAP) 5/325 mg (Mallinckrodt Inc., USA) for rescue analgesia when NRS score > 4 after receiving four times of bolus with the PCA device. OC/APAP will be prescribed at an interval of at least 6 h until the end of our study. Total doses of rescue analgesia consumed will be recorded.

### Follow-up

Follow-up will last 3 months postoperatively, during which an independent researcher blinded to the patient’s group allocation will conduct the following evaluations at different time points: pain NRS, sufentanil consumption in the PCA device, time to first PCA demand button press, cumulative consumption of OC/APAP, PONV scores, wound healing scores, World Health Organization QoL abbreviated version (WHOQOL-BREF), Patient and Observer Scar Assessment Scale (POSAS) scores, etc [34]. Adverse effects related to the surgery, anesthesia, steroid, or analgesics will be monitored and documented. Follow-up will be performed by telephonic communication after discharge, at 1 and 3 months postoperatively.

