#### Secondary outcome

Pain NRS scores at 2, 4, 12, 48, and 72 h after craniotomy;

Prolonged post-craniotomy pain NRS at 1 and 3 months;

Number of patients needing no sufentanil at 24, 48, and 72 h after craniotomy;

Total consumption of sufentanil with PCA device at 24, 48, and 72 h postoperatively;

Total number of times that patients press the PCA button, including valid and invalid presses at 24, 48, and 72 h postoperatively;

Time to first PCA button press after surgery;

Time to first rescue analgesia with OC/APAP after surgery;

Duration of hospitalization postoperatively.

PONV scores at 24, 48, and 72 h after surgery. PONV is rated by patients as 0, absent; 1, nausea not requiring treatment; 2, nausea requiring treatment; and 3, vomiting.

WHOQOL-BREF scores at 1 and 3 months after craniotomy. The WHOQOL-BREF is a questionnaire of 26 items, including social relationships (3 items), physical health (7 items), psychological health (6 items), environment (8 items), overall QoL (1 item), and general health (1 item). Each domain’s mean score can range between 4 and 20 with a higher score indicating a better QoL.

Local soft-tissue atrophy at 72 h, 1 and 3 months after craniotomy. It is presented as superficial atrophy of skin and adipose tissue, central discoloration of the skin, yellow subcutaneous deposits, small sebaceous glands, cessation of hair growth, or mauve colored periphery at the injection site.

Wound healing score at 72 h, 1 and 3 months postoperatively. Wound Healing Score is rated by an independent researcher as excellent, good, and suboptimal.

Patient and Observer Scar Assessment Scale (POSAS) at 72 h, 1 and 3 months after craniotomy [35]. POSAS consists of 2 numerical numeric scales, the observer component, and the patient component.

Other complications such as respiratory depression, allergic reaction, local or systemic toxicity, wound infection, hematoma, and injection site infection throughout the treatment and follow-up period.

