### Safety assessment

In this study, adverse events (AEs), defined as negative or unintended clinical manifestations throughout the treatment and follow-up period, will be monitored and recorded in detail on a case report form (CRF). All AEs related to the surgery, anesthesia, steroid, or analgesics, together with the soft-tissue atrophy and local infection, which might be induced by scalp infiltration with the mixture of ropivacaine and D-PAL emulsion, should be monitored during the 3 months’ follow-up. The soft-tissue atrophy, clinically manifested as superficial atrophy of skin and adipose tissue, central discoloration of the skin, yellow subcutaneous deposits, small sebaceous glands, cessation of hair growth, or mauve-colored periphery at the site of injection [36], will be monitored by careful observation and will be evaluated partly by the Patient and Observer Scar Assessment Scale (POSAS) and Wound healing score at 72 h, 1 m, and 3 months after craniotomy. AEs will be treated and reported to the Institutional Review Board (IRB) as soon as possible. Study interventions-related AEs will be treated for free. The trial will be terminated immediately in case of serious life-threatening AEs leading to prolonged hospital stay or death.

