## Data collection and management

Data collection and management will be performed via the hospitalized medical record system or CRF by an independent researcher. All data will be kept strictly confidential for research purposes only. Only the primary investigator can obtain final test data. Follow-up will be conducted on days 1, 2, and 3 and at months 1 and 3 by an independent and experienced researcher, either in person or by contact via telephone (after discharge). Participants who discontinue or deviate from intervention protocols will not be replaced. They will be allowed to withdraw their consent without any restriction at any time. Their data will be retained, including all the primary and secondary outcomes until termination, except for the cases that are unable to complete the assessment of the primary outcome at 24 h postoperatively.

All personal information and data about the participants will be recorded into the CRFs, which are coded by an identification number and stored in a secure cabinet throughout the trial to guarantee confidentiality. All data will be entered into the Excel form for analysis by two independent researchers with double-checking. The electronic data will be stored on a double password-protected computer. Only the primary investigator and the statistician will have access to the files.

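### Observer-rated wound and scar outcomes are scheduled at 1 and 3 months, when the only stated contact is by telephone

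*Protocol article*

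**What the plan says.** **Mode of contact.** The protocol article describes it twice.

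- Follow-up section: "Follow-up will be performed by telephonic communication after discharge, at 1 and 3 months postoperatively". The same paragraph lists wound healing scores and POSAS among the evaluations made by the blinded researcher.
- Data collection and management: for the first three days and for both later times alike, contact is "either in person or by contact via telephone (after discharge" (the bracket closes there).

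**What is to be measured.** The Secondary outcome section sets three times (72 h, 1 month, 3 months) and, in part, the rater.

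- The wound score is due at all three times. Its rater is named: "Wound Healing Score is rated by an independent researcher as excellent, good, and suboptimal".
- The scar scale is due at all three times. Its structure is given: "POSAS consists of 2 numerical numeric scales, the observer component, and the patient component".
- Local soft-tissue atrophy is due at all three times, defined by changes in the skin, underlying fat and hair at the injection site. No rater is named.

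The Safety assessment section keeps the same schedule for atrophy and says how it is to be found: it "will be monitored by careful observation and will be evaluated partly by the Patient and Observer Scar Assessment Scale (POSAS"). The other instrument named there is the wound score.

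**The concern.** A wound score given by a researcher and the observer half of a scar scale both need someone other than the patient to look at the scalp. A telephone call does not provide that. The article thus fixes a mode of follow-up and also fixes outcomes which that mode cannot deliver.

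This matters because local tissue harm is the safety question the protocol itself singles out. The Safety assessment section names soft-tissue atrophy and local infection as possible effects of infiltrating the mixture. The Discussion explains how steroid and local anaesthetic mixtures might produce depressed, atrophic skin and says few trials exist. It also defends the 3-month follow-up with tissue atrophy in mind. The 1- and 3-month ratings are the part of the schedule that serves this question beyond the first days.

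The Statistics section plans to compare the wound healing score and POSAS between groups at the different time points, so the analysis expects these values to exist.

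**Working it through.** No sample-size, power or alpha figure is involved. The check sets the mode of contact beside the requirements of each outcome and counts the cells in conflict.

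**Inputs**

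- Assessment times for the three local outcomes: 72 h, 1 month, 3 months (Secondary outcome; Safety assessment).
- Contact at 1 and 3 months: telephone, after discharge (Follow-up).
- Rater: independent researcher for the wound score; an observer for one of the two POSAS scales; none named for atrophy, whose method is observation (Secondary outcome; Safety assessment).

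**Outcome by time**

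| Outcome | 72 h | 1 month | 3 months |
|---|---|---|---|
| Wound healing score (researcher) | can be seen | conflict | conflict |
| POSAS observer scale | can be seen | conflict | conflict |
| Soft-tissue atrophy (observation) | can be seen | patient description only | patient description only |
| POSAS patient scale | obtainable | obtainable | obtainable |

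**Count over the first three rows**

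- All cells: 3 outcomes × 3 times = 9.
- Clear conflict, because a non-patient rater is specified: 2 outcomes × 2 times = 4.
- Weakened, because observation is specified without a named rater: 1 outcome × 2 times = 2.
- Unaffected, at 72 h: 3 outcomes × 1 time = 3.
- Check: 4 + 2 + 3 = 9.

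**Does the second statement of mode resolve the conflict?** The sentence in Data collection and management covers days 1 to 3 and months 1 and 3 together, and offers a visit or a call. Its bracket attaches the telephone to the period after discharge. The natural reading is in person while the patient is in hospital and by telephone afterwards, which agrees with the Follow-up section. If it is read instead as allowing visits at 1 and 3 months, it disagrees with the Follow-up section and leaves the mode open. Neither reading states how the scalp will be seen.

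**Would the missing-data method repair it?** The Missing data section relies on multiple imputation throughout. Imputation borrows from patients in whom the value was observed. If an observer rating is absent at 1 and 3 months in essentially everyone, nothing at those times is available to inform the imputation model.

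**The case against.** **Condensation.** A journal article shortens the full protocol, and the schedule figure is not shown. Photographs, video or routine clinic review may be described elsewhere, and contact by telephone does not by itself rule out sending an image. This has weight: it is why the claim is that the article gives no route to visual assessment, and not that assessment is impossible in practice. It does not remove the point, because the conflict lies between statements the article does make.

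**Atrophy.** No rater is named, and a patient could notice and report some of the listed signs, such as discoloration or loss of hair growth. This stands. Atrophy is therefore counted separately from the four clear cells. A description over the telephone is still weaker than the observation that the Safety assessment section specifies. Patients are blinded to allocation, so the main worry is missed or unstandardised findings more than a difference in reporting between the groups.

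**Importance.** These are secondary safety outcomes. The limitations in the Discussion already say the sample is too small to identify rare harms, including changes in wound healing, and suggest longer follow-up if atrophy or infection occurs. Adverse events are still collected throughout. All of this limits the severity. None of it addresses how the ratings are made.

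**Stronger readings that a reader might infer**

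- *That the 72 h rating is worthless, because neither scar nor atrophy could have developed by then.* The article does not give a time to onset; its remark about months to years concerns recovery.
- *That patients' accounts would be recorded as if they were observer ratings.* That is a guess about conduct. The documents support only that the ratings would be absent or replaced by something else.
- *That all six later cells are equally unobtainable.* The article does not make atrophy strictly observer-rated, so two of the six are weakened and not excluded.

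**Conclusion.** The conflict is real and lies in the stated text. As written, the wound healing score and the POSAS observer scale cannot be rated as specified at 1 and 3 months (four cells), and soft-tissue atrophy at those times would depend on what the patient describes (two cells). Followed to the letter, the plan would leave little basis for any observer-rated statement on local tissue safety after 72 h.

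The conclusion rests on two assumptions: that the telephone statement in the Follow-up section governs both later contacts, and that the 72 h assessment is made while the patient can be seen. The article supports the second by listing day 3 among the follow-up days and tying the telephone to the period after discharge, but it does not state a discharge time.

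The pain scores, WHOQOL-BREF, POSAS patient scale, 72 h ratings, primary outcome and sample size are untouched. This should be corrected, but it does not threaten the trial's main analysis.

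**What to change.** Reconcile the Follow-up and Data collection and management sections with the Secondary outcome and Safety assessment sections in one of two ways.

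1. **Keep the outcomes and provide a view of the scalp.** State that the blinded researcher rates the wound healing score, the POSAS observer scale and atrophy at 1 and 3 months from a standardised photograph or a video call, or in person where the patient attends. Record the mode for each rating. The cost is an image instruction added to contacts already planned; ratings from images are less precise than examination.
2. **Keep the telephone and narrow the outcomes.** Limit the 1- and 3-month local outcomes to the POSAS patient scale and patient-reported wound or skin problems, keep the observer ratings at 72 h only, and make no observer-rated claim at the later times. The cost is a shorter list of outcomes and a weaker statement on local safety.

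The Trial status section says recruitment has not begun, so either change can be made before the first patient. A rating not taken at its time point cannot be recovered later.

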### Outcome measures

#### Baseline data

The demographic characteristics include age, gender, BMI, ASA status, neurological pathology, and comorbidity. Surgery and anesthesia characteristics include surgical site, length of incision, volume of local infiltration solution, duration of surgery and anesthesia, intraoperative analgesics (sufentanil and remifentanil) consumption, perioperative hemodynamic parameters, cumulative intravenous dexamethasone prescribed by a neurosurgeon, etc.

#### Primary outcome

Primary outcome will be the pain NRS scores at 24 h after craniotomy.

#### Secondary outcome

Pain NRS scores at 2, 4, 12, 48, and 72 h after craniotomy;

Prolonged post-craniotomy pain NRS at 1 and 3 months;

Number of patients needing no sufentanil at 24, 48, and 72 h after craniotomy;

Total consumption of sufentanil with PCA device at 24, 48, and 72 h postoperatively;

Total number of times that patients press the PCA button, including valid and invalid presses at 24, 48, and 72 h postoperatively;

Time to first PCA button press after surgery;

Time to first rescue analgesia with OC/APAP after surgery;

Duration of hospitalization postoperatively.

PONV scores at 24, 48, and 72 h after surgery. PONV is rated by patients as 0, absent; 1, nausea not requiring treatment; 2, nausea requiring treatment; and 3, vomiting.

WHOQOL-BREF scores at 1 and 3 months after craniotomy. The WHOQOL-BREF is a questionnaire of 26 items, including social relationships (3 items), physical health (7 items), psychological health (6 items), environment (8 items), overall QoL (1 item), and general health (1 item). Each domain’s mean score can range between 4 and 20 with a higher score indicating a better QoL.

Local soft-tissue atrophy at 72 h, 1 and 3 months after craniotomy. It is presented as superficial atrophy of skin and adipose tissue, central discoloration of the skin, yellow subcutaneous deposits, small sebaceous glands, cessation of hair growth, or mauve colored periphery at the injection site.

Wound healing score at 72 h, 1 and 3 months postoperatively. Wound Healing Score is rated by an independent researcher as excellent, good, and suboptimal.

Patient and Observer Scar Assessment Scale (POSAS) at 72 h, 1 and 3 months after craniotomy [35]. POSAS consists of 2 numerical numeric scales, the observer component, and the patient component.

Other complications such as respiratory depression, allergic reaction, local or systemic toxicity, wound infection, hematoma, and injection site infection throughout the treatment and follow-up period.

### Sample size

Earlier studies have reported that incision-site infiltration with ropivacaine plus dexamethasone could reduce about 30-50% of postoperative pain severity compared with ropivacaine alone [6, 19, 22]. Based on these literatures and our clinical experience, we hypothesize that the pain NRS scores was approximately 2.0 ± 1.5 (mean ± standard deviation) scores in the ropivacaine alone group and attempt to detect a difference of 40% in pain NRS scores between groups at 24 h after craniotomy. Therefore, the pain scores would be about 1.2 ± 0.9 scores in D-PAL plus ropivacaine group at 24 h after craniotomy. PASS V.11 software (NCSS, Kaysville, UT, USA) is used for sample size calculation with *α* = 0.05, *β* = 0.1, and power = 90%. Considering a dropout rate of 20%, a total of 130 patients will be required in this trial (*n* = 65 per group).

